#### **4. Objectives**

The major objective of the proposed study is to demonstrate the suitability of new markers for folate status in humans, which avoid blood sampling, as required for the established marker RBC folate concentration, but can be obtained from spot urine samples.

Specific hypotheses to be tested:

Correlation study:

- a) The 24 h urinary excretion of total p-ABG, as extrapolated via urinary creatinine concentration from the total p-ABG concentration in a spot sample is significantly correlated to RBC and plasma folate levels in the studied subjects
- b) The 24 h urinary excretion of FIGLU, as extrapolated via urinary creatinine concentration from the FIGLU concentration in a spot sample is significantly correlated to RBC and plasma folate levels in the studied subjects

Intervention study:

- a) changes in folate status (RBC folate) after supplementary intake of folate result in increased urinary excretion of total p-ABG and FIGLU in subjects identified with a low folate status and in subjects identified with a high folate status among the study participants of the correlation study

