#### **5. Participating subjects**

##### **5.1. Subject number**

The sample size estimation is based the correlation study. It is assumed that a correlation of at least 0.35 would be sufficient to use urinary total p-ABG or FIGLU as markers for

folate status. To detect such a correlation as statistically significant with a power 80% and  $\alpha$  of 0.05 samples from 49 subjects have to be analyzed (Uitenbroek, Daan G, Binomial. SISA. 1997. <http://www.quantitativeskills.com/sisa/distributions/binomial.htm>. (1 Jan. 2004). Thus, 50 subjects will be enrolled into the correlation study and from these participants for the intervention study will be selected.

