## 9. Data management and biometrical evaluation

All clinical data will be recorded in specifically prepared forms to be incorporated later into an electronic database. In the database they will be combined with the results of the laboratory analyses.

For all quantitative parameters determined a test for normal distribution will be performed according to Kolmogorov-Smirnov. If normal distribution can be assumed, mean and standard deviation will be given for these parameters. For non normally distributed data median and interquartile range will be provided and data will be transformed appropriately prior to statistical analysis.

The repeated basal determination of blood markers of folate status is performed, as it is reasoned that both parameters undergo not only random variation, but there might be trends over time, after changes of dietary habits or physiological status. The effect of these trends should be attenuated by application of the average values of two measurements taken at different time points. This should become obvious from a better correlation of the averaged values compared to the individual values. A similar reasoning is behind the complete 24h urine collection, if there are short term variations in urinary concentration of total p-ABG or FIGLU extrapolation to total volume of excretion during 24 hours via urinary creatinine concentration is not adequate. If this is the case, there should be a closer relationship between the measured 24 h excretion of p-ABG and FIGLU with RBC folate than between the 24 h excretion estimated from the spot urine sample and RBC folate.

The major focus of statistical evaluation is a correlation and receiver operator characteristics (ROC) (Streiner et al, 2007) analysis between the determined circulating folate status markers and the urinary markers of folate status. Correlation analysis will be performed according to Pearson or Spearman. For ROC analysis classification into the lowest quartile as assessed with RBC folate will be set as "Gold Standard". Corresponding specificity, sensitivity, positive predictive value and negative predictive value will be determined for urinary total p-ABG and FIGLU excretion (measured and estimated 24 h excretion). Parameters will be compared in respect to the area under the ROC curve.

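### The 49 subjects in section 5.1 give 80% power for r = 0.35 only under a one-sided test that the protocol never declares; two-sided, the planned 50 give about 71%

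*Protocol*

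**What the plan says.** Section 5.1 bases the sample size on the correlation study. The effect to detect is given as: "It is assumed that a correlation of at least 0.35 would be sufficient to use urinary total p-ABG or FIGLU as markers for" folate status. The error rates and the result follow: "To detect such a correlation as statistically significant with a power 80% and" an alpha "of 0.05 samples from 49 subjects have to be analyzed". The conclusion drawn is: "Thus, 50 subjects will be enrolled into the correlation study". The source cited is a web calculator whose title and address refer to the binomial distribution. Section 5.1 does not say whether alpha is one-sided or two-sided.

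Section 4 words correlation hypotheses a) (total p-ABG) and b) (FIGLU) alike: the 24 h excretion estimated from a spot sample "is significantly correlated to RBC and plasma folate levels in the studied subjects". Neither names a direction. Section 9 gives the test without sidedness: "Correlation analysis will be performed according to Pearson or Spearman". It then makes the coefficients obtained the primary criterion for whether a marker is applicable.

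**The concern.** A correlation test with an undirected hypothesis and an unqualified alpha of 0.05 is ordinarily read as two-sided. On that reading 49 subjects looks too few for r = 0.35 at 80% power.

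This is the only power statement in the protocol. If it holds only under an assumption that the reader cannot see, a marker that truly meets the protocol's own threshold of 0.35 would miss significance more often than the 20% that section 5.1 implies. A null result would then look like stronger evidence against the marker than it is.

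**Working it through.** **Inputs.** r = 0.35 against 0, power 80%, alpha 0.05, stated N = 49 and enrolled N = 50 (all section 5.1). Sidedness is not given. Normal quantiles: 1.645 (one-sided 0.05), 1.960 (two-sided 0.05), 0.842 (80% power).

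**Formula.** Fisher z: N = ((z_alpha + z_power) / atanh(r))² + 3, with atanh(0.35) = 0.3654.

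**Reproducing the stated figure**

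- One-sided: ((1.645 + 0.842) / 0.3654)² + 3 = 46.3 + 3 = 49.3. This is 49 when rounded, 50 when rounded up, and 49 with the small bias term r/(2(N−1)). The stated figure reproduces.
- Two-sided: ((1.960 + 0.842) / 0.3654)² + 3 = 58.8 + 3 = 61.8. This is 62, or 61 with the bias term.
- Other two-sided approximations give 58.8 (without the +3), 64.1 (r in place of atanh r) and 58.2 (based on (1−r²)/r²). None comes near 49.

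**Power at the planned size.** Power = Φ(atanh(r)·√(N−3) − z_alpha). At N = 50, 0.3654 × √47 = 2.505.

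- Two-sided: Φ(2.505 − 1.960) = Φ(0.545) = 70.7%.
- One-sided: Φ(2.505 − 1.645) = Φ(0.860) = 80.5%.

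| N | One-sided, Fisher z | One-sided, simulated | Two-sided, Fisher z | Two-sided, simulated |
|---|---|---|---|---|
| 49 | 79.8% | 80.7% | 69.8% | 70.7% |
| 50 | 80.5% | 81.4% | 70.7% | 71.5% |
| 61 | 87.2% | 87.8% | 79.5% | 80.2% |
| 62 | 87.7% | 88.3% | 80.2% | 80.8% |

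The simulation applies the t test for Pearson's r to 400,000 bivariate normal samples. A noncentral t approximation is somewhat more generous (73.5% two-sided at N = 50) but still well short of 80%.

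**Correlation detectable with 80% power, two-sided, N = 50.** tanh((1.960 + 0.842) / √47) = tanh(0.409) = 0.387. By simulation, power is 79.2% at r = 0.38 and 80.2% at r = 0.385. The detectable value is therefore about 0.38, at the upper end of that rounding.

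**Spearman, which section 9 also allows.** For an underlying bivariate normal correlation of 0.35 and N = 50, simulated power is about 66% two-sided and 77% one-sided.

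**Can a one-sided test be read from the text?** Section 4 does write a direction into its intervention hypothesis, where excretion of both markers is expected to increase after supplementation. It leaves the two correlation hypotheses undirected. For FIGLU the direction is also inconsistent. Sections 1 and 3 describe excretion as raised in folate deficiency after a histidine load, which points to a negative correlation with folate status. The intervention hypothesis in section 4 expects FIGLU to rise with supplementation, which points the other way.

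**The case against.** The strongest reply is that nothing has been miscalculated: the inputs in section 5.1 give 49 by a standard formula. The rationale also carries some direction. Sections 1 and 3 lead the reader to expect more total p-ABG with more folate, and section 5.1 speaks of a minimum useful correlation. For p-ABG at least, a one-sided test is plausible, and under it the stated power is delivered. Sidedness is also often fixed in a statistical analysis plan, and reading an unqualified alpha as two-sided is a convention that the protocol does not itself state.

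Much of this stands. A reader might infer an arithmetic error, and the documents do not support that. Nor does the binomial citation show that no correlation calculation was done: the agreement with 49.3 suggests one was, and what the cited page contains cannot be checked here. A reader might also infer that a missed p-value would sink a marker. Section 9 makes the coefficients the primary criterion and adds ROC area, sensitivity, specificity and predictive values, so significance is only part of the decision.

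What does not stand is leaving the matter to a later document. Section 5.1 itself states alpha, power and N. If a later plan specified the usual two-sided test, the 80% given here would become wrong. For FIGLU, no single direction can be taken from the text to support a one-sided test.

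**Conclusion.** The point holds as one of an undeclared assumption. The 49 subjects and 80% power in section 5.1 are correct for a one-sided alpha of 0.05, which the protocol does not declare and which its undirected correlation hypotheses do not imply. Under a two-sided alpha of 0.05, power for r = 0.35 with 50 subjects is about 71%. The chance of missing a marker at the threshold is then about 29%, not 20%.

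These figures assume bivariate normality, Pearson's r and all 50 subjects analysed. Power is lower with Spearman. It does not follow that the study must enrol more subjects: the two-sided shortfall amounts to a detectable correlation of about 0.38 in place of 0.35, which can simply be stated. If one-sided tests were intended, 50 subjects suffice as planned for Pearson's r, but the protocol has to say so.

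**What to change.** Preferred: keep n = 50 and restate section 5.1 along these lines: *with 50 subjects and a two-sided alpha of 0.05, the power is about 71% for r = 0.35 and 80% for r of about 0.38.* Replace the calculator reference with one that matches a correlation calculation, since the title and address given refer to a binomial-distribution page.

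Alternative: declare one-sided tests at 0.05 and write the direction into hypotheses a) and b) in section 4. For FIGLU this requires first reconciling sections 1 and 3 (excretion raised in deficiency after a histidine load) with the intervention hypothesis in section 4 (excretion expected to increase after supplementation). Otherwise section 4 would contradict itself.

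The preferred option costs a sentence and a reference, with no extra subjects and no change to the analysis. Its downside is a less favourable stated power.

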## 5.2 Selection criteria and recruitment

The subjects to participate will be contacted by advertisement on the campus of the University of Munich, by announcing the study on the website of the university hospital and if needed by newspaper advertisement. For enrollment subjects have to fulfill the following inclusion criteria:

- age: 18 – 45 years
- apparently healthy
- normal results on haematologic pattern and blood chemistry tests (according to university hospital reference values)
- plasma vitamin B12 > 160 pmol/l
- no diagnosis of intestinal, renal or thyroid disease (self reported)
- only male subjects will be enrolled but regular consumption of vitamin supplements (including folate) is not an exclusion criterium, as we aim to cover a wide range of folate concentrations.

On the other hand, conditions, which are expected to influence folate catabolism are exclusion criteria:

- recent (3 months) treatment with medication, assumed to interfere with folate status
- abuse of alcohol or drugs

## 6. Study Procedure

The study consists of two consecutive parts (Fig. 1). During the initial correlation study the relationship between established markers of folate status and the newly proposed markers (urinary FIGLU and urinary total p-ABG) is investigated. From the subjects participating in the correlation study, persons with low and high folate status will be selected for participation in the intervention study.

[figure not shown]

Figure 1: Overview about the study procedure including the correlation study and the intervention study, which involves only selected subgroups of the participants of the correlation study

Potential subjects will contact the study center via telephone and during the telephone conversation eligibility criteria will be preliminarily checked and questions of the subjects in respect to the study procedure and associated burden will be answered. If criteria seem fulfilled and the person intends to participate an appointment will be made for obtaining informed consent and if obtained blood and urine will be sampled. These appointments will be before 9:00 in the morning (to obtain fasted blood samples) in the Dr. von Hauner Children Hospital. At this initial appointment blood and spot urine will be collected. Furthermore the subjects are provided with a questionnaire on their dietary habits, with a focus on folate containing food stuffs and vitamin supplements. The questionnaire will also cover any medication taken and principle parameters of a physical examination and anthropometry will be recorded. The completed questionnaire will be brought back at the second blood sampling appointment, which will be scheduled 3 weeks later also early in the morning. The subjects will also be given a suitable container for a full 24 urine collection. Starting in the morning on the day before the second blood sampling subjects start a complete urine collection and hand over the urine to the study personal at the second blood sampling appointment, which follows the same procedure as the first appointment. The questionnaire will be briefly discussed with the subjects to clarify any obvious ambiguities.

## 6.1 Correlation study

### Detailed planning:

1. Interested subjects will call the study center for preliminary discussion of the study and eligibility criteria; if the subject seems eligible and intends to participate details for the first appointment will be agreed and instructions will be given

2. First appointment (before 9.00 am after a 12 hour fasting period):

- written informed consent form will be obtained (covering correlation study and intervention study)
- physical examination and clinical questionnaire will be completed
- collection of cheek cells with a sterile swab (09-511-5006/2, nerbe plus GmbH) according to clinical routine and storage of the sample at -20°C
- fasted blood will be collected by venipuncture (serum: S-Monovette 05.1104, 4.5 ml, EDTA blood: S-Monovette, 4.9 ml)

EDTA- blood for hematology and analyses from whole blood will be taken away and the remaining blood samples will be centrifuged (4°C, 1400g, 5 min) to obtain serum and plasma, which will be transferred to the respective laboratories or frozen at -80°C for storage and later analysis

- spot urine will be collected in a brown 100 ml beaker (Sarstedt: 75.562.011) and 3 aliquots (10 ml each, Sarstedt 10.252.030) will be frozen for later analysis at -20°C
- questionnaire on dietary habits (focus on folate intake) will be handed over to the subjects for completion and returning at the second appointment
- container (2.0 l, Sarstedt 77.580, containing 5 g ascorbate to prevent folate breakdown) and instructions for 24h urine collection will be handed over to the subject

3. Second appointment (before 9.00 am, after a 12 h fasting period, 3 weeks after first appointment):

- dietary questionnaire will be returned and checked for plausibility
- 24h urine container returned, the volume of urine will be recorded and after thorough mixing 3 aliquots (10 ml each, Sarstedt 10.252.030) will be frozen for later analysis at -20°C
- additionally spot urine will be collected in a brown 100 ml beaker (Sarstedt: 75.562.011) and 3 aliquots (10 ml each, Sarstedt 10.252.030) will be frozen for later analysis at -20°C
- fasted blood will be collected by venipuncture (serum: S-Monovette 05.1104, 4.5 ml, EDTA blood: S-Monovette, 4.9 ml)

EDTA- blood for hematology and for analyses from whole blood will be taken away and

the remaining blood samples will be centrifuged (4°C, 1400g, 5 min) to obtain serum and plasma, which will be transported to the respective laboratories or frozen at -80°C for storage and later analysis

- subjects qualifying for the intervention study will be enrolled (see 6.2.)

## 6.2 Intervention study

The part of the study described so far (correlation study) relates to the evaluation of the principal relationship between urinary excretion of total p-ABG and FIGLU and blood markers of folate status, which is needed for the evaluation of the suitability of these markers as screening tools and as proxies for folate status. The second part (intervention study) shall clarify, whether total p-ABG and FIGLU excretion are suitable for the determination of changes in folate status after increased intake of folic acid starting from relatively high or low levels.

From those subjects, who do not already take supplements, 15 persons each from the highest and lowest quartile in respect to RBC folate status (based on RBC folate concentration at the first appointment) will be asked to participate in a 12 week supplementation study. The participating subjects will be given a folate supplement, providing 400 µg of folic acid per day. For the evaluation of the time course of the blood and urine markers of folate status after 6 weeks and after 12 weeks blood and urine samples will be obtained. During the intervention period subjects will be contacted by telephone regularly to discuss questions and to enhance adherence to the protocol.

### 1. Second appointment (continued):

- subjects (n=20, 10 each for the highest and lowest quartile of RBC folate status) who participate in the intervention study will be given a pack with 50 tablets (400 µg folate/tablet) of a commercially available folate supplement
- a brief questionnaire to note any unusual events or complaints will be provided
- container (2.0 l, Sarstedt 77.580, containing 5 g ascorbate to prevent folate breakdown) and instructions for 24h urine collection will be handed over to the subject (if collection of spot samples is found useful in the correlation study spot samples will be collected instead of the 24h urine)
- a third appointment about 6 weeks later will be scheduled

### 2. Third appointment (intervention study participants only, before 9.am after a 12 h fasting period, 6 weeks after second appointment)

- questionnaire on events will be discussed

- the urine container will be returned, the volume of urine will be recorded and after thorough mixing 3 aliquots (10 ml each, Sarstedt 10.252.030) will be frozen for later analysis at -20°C
- fasted blood will be collected by venipuncture (serum: S-Monovette 05.1104, 4.5 ml, EDTA blood: S-Monovette, 4.9 ml)  
EDTA- blood for hematology and analyses from whole blood will be taken away and the remaining blood samples will be centrifuged (4°C, 1400g, 5 min) to obtain serum and plasma, which will be transported to the respective laboratories or frozen at -80°C for storage and later analysis
- the left over tablets will be counted and the participants will be given a second pack with 50 tablets (400 µg folate/tablet) of a commercially available folate supplement
- a fourth appointment about 6 weeks later will be scheduled

3. Fourth (final) appointment (intervention study participants only, before 9.am after a 12 h fasting period, 6 weeks after third appointment)

- questionnaire on events will be returned and discussed
- the urine container will be returned, the volume of urine will be recorded and after thorough mixing 3 aliquots (10 ml each, Sarstedt 10.252.030) will be frozen for later analysis at -20°C
- fasted blood sample will be collected by venipuncture (serum: S-Monovette 05.1104, 4.5 ml, EDTA blood: S-Monovette, 4.9 ml)  
EDTA- blood for hematology and analyses from whole blood will be taken away and the remaining blood samples will be centrifuged (4°C, 1400g, 5 min) to obtain serum and plasma, which will be transported to the respective laboratories or frozen at -80°C for storage until later analysis
- not consumed supplement tablets will be returned and counted

## **7. Study supplement**

The study supplement will be folate containing tablets approved as non prescription vitamin supplement, which provide 400 µg folate per tablet (Folverlan® 0.4mg, Verla-Pharm Arzneimittel, 82234 Tutzing). The subjects will consume one tablet per day.

## **8. Laboratory analyses:**

Analyses will be conducted in the Labor für Stoffwechsel und Ernährungsforschung at the Dr. von Hauner Children Hospital of the University of Munich or in the central laboratories of the Dr von Hauner Children's Hospital or the University Hospital, respectively.

- a) full blood count and blood chemistry (ALAT, ASAT) will be determined at the central laboratory of the Children's Hospital according to established routine procedures
- b) serum vitamin B12 concentration will be determined in the central laboratory of the university hospital by competitive protein binding and electro-chemiluminescence applying a commercial assay (Roche Elecsys; Mannheim, Germany)
- c) plasma vitamin B6 (pyridoxine) will be determined in the central laboratory of the university hospital by HPLC applying a commercially available assay (Chromsystems, Munich, Germany), 300 µl EDTA plasma are required for analysis (transport at 4°C with protection against light)
- d) serum folate will be determined in the central laboratory of the university hospital by competitive protein binding and electro-chemiluminescence applying a commercial assay (Immolite 2000, Siemens ; Munich, Germany) .
- e) RBC folate will be determined in the central laboratory of the university hospital by competitive protein binding and electro-chemiluminescence after lysis and dilution of the full blood applying a commercial assay (Immolite 2000, Siemens ; Munich, Germany)
- f) plasma homocysteine will be determined in the central laboratory of the university hospital from EDTA blood using a competitive immunoassay employing direct chemiluminescence (ADVIA Centaur Homocystein Assay, Siemens Healthcare, Deerfield, USA). The samples will be frozen at -80° and transported and analysed in batches.
- g) urinary creatinine will be determined at the central laboratory of the children's hospital according to established routine procedures
- h) urinary FIGLU analysis will be done in the Labor für Stoffwechsel und Ernährungsforschung by LC-MS/MS based on the procedure described by (Bishop et al, 2007)
- i) urinary total p-ABG (Ap-ABG and p-ABG) will be determined in the Labor für Stoffwechsel und Ernährung using a LC-MS/MS method modified from Sokoro et al (Sokoro et al, 2006)
- j) urinary methylmalonic acid will be analysed in the Labor für Stoffwechsel und Ernährungsforschung by LC-MS/MS

